### Statistical analysis

The modelling strategy will adhere to intention-to-treat principles. Characteristics of participants and baseline levels of study outcomes across arms will be compared descriptively at baseline to examine potential confounding and to ensure that randomization was successful. Treatment effects will be estimated with generalized logistic mixed models specified to compare differences in primary outcome from baseline to follow-up, and baseline to 18-months post. A random effect for cluster (VDC) will be included to account for within-group clustering, and degrees of freedom will be properly calculated. Time, condition, and time by condition interaction will be fit as fixed effects. To the extent necessary, estimates will be adjusted for socio-demographic characteristics should confounding be detected. Additional quantitative analyses using mixed models will be employed to investigate mediation [39] and adherence. Missing data will be handled using full information maximum likelihood [40].

Transcripts will be generated from audio recordings of FGDs, interviews and open ended IVR responses. An analysis team comprised of the PI and select EA staff will analyse the transcripts using a mixture of deductive and inductive coding approaches, analytic memos, and matrix and network displays [41]. Analysis team members will independently read the transcripts and contribute to a collective draft codebook and series of memos, which are separated into process and analytic components. Analysis will examine the occurrence, dynamics, and pathways to change with a particular emphasis on differences by location, caste, and socioeconomic status. Qualitative analyses will additionally seek to identify any other characteristic or contextual feature that is revealed to be a potential modifying factor of the intervention impact or explanation for null findings. Findings from the qualitative data analysis will inform subsequent quantitative subgroup analyses. Qualitative and quantitative findings will be iteratively fed back into the analysis of the other to generate rich, contextualized results and findings from both processes will be jointly presented in manuscripts to the extent possible.

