## Methods/design

The study utilizes a concurrent mixed methods design which capitalizes on the strengths of both qualitative and quantitative data collection techniques to ascertain project effectiveness. This study design will also document participant and stakeholder experiences, as well as investigate the mechanisms of action and contextual factors that could affect the outcomes and/or explain results [15]. The quantitative aspect of the evaluation is a pair-matched, repeated cross-sectional 2-armed, single-blinded trial (RCT: *N* = 36 clusters [Village Development Committees)], 1440 individuals), comparing a social behaviour change communication (SBCC) strategy to radio programming alone for its impact on physical and / or sexual IPV at the end of programming (12 months post-baseline; February-March 2017) and 6-months post the cessation of project activities (18-months post baseline; September-October 2017). The qualitative aspects of the design include several longitudinal approaches to understand the impact of the intervention and examine mechanisms of change, including in-depth interviews with participants (*N* = 18 couples), and focus group discussions with community leaders (*N* = 3), and family members of participants (*N* = 12). Measurement activities are timed (Fig. 1) to enable iterative and parallel data analysis. The combined methodology, along with data collected through ongoing monitoring of intervention activities, will offer a rigorous test of the intervention and provide information to inform scale-up and replication efforts.

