### Sample size and power

This study is powered to detect meaningful differences in prevalence of IPV. To calculate study power, we took into consideration the number of experimental conditions, the number groups/clusters nested within conditions, the number of persons within groups, the intra-class correlation coefficient (ICC), within-group over time correlations, and traditional variance components [38]. We have 36 units of randomization (VDCs) and 40 randomly sampled persons within each unit, 20 in each of two selected VDC sub-units called wards. Assuming a conservative over-time group-level correlation of 0.40, a 12-month prevalence of physical or sexual IPV of 14%, which was based on estimates from the 2011 Demographic and Health Survey in Nepal [2]. a conservative standard deviation of 25%, a conservative intra-class correlation of 0.05, with 80% power and 5% alpha (2 sided test) the study can detect a difference in percentage of 7%.

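### The primary model names a single VDC random effect, which contradicts the over-time correlation of 0.40 used for power; the time-by-condition test then has a type I error of about 13 to 19% under the plan's inputs

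*Protocol article*

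**What the plan says.** The design is a "pair-matched, repeated cross-sectional 2-armed, single-blinded trial" (Methods/design), with surveys at baseline, 12 months and 18 months.

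The Statistical analysis section states the primary model in three sentences. The estimand is a change from baseline: "Treatment effects will be estimated with generalized logistic mixed models specified to compare differences in primary outcome from baseline to follow-up, and baseline to 18-months". The random part is: "A random effect for cluster (VDC) will be included to account for within-group clustering, and degrees of freedom will be properly calculated". The fixed part is: "Time, condition, and time by condition interaction will be fit as fixed effects". No VDC-by-time effect, random slope, cluster-period term or robust variance is named.

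The Sample size and power section gives: "We have 36 units of randomization (VDCs) and 40 randomly sampled persons within each unit, 20 in each of two selected VDC sub-units called wards". It continues: "Assuming a conservative over-time group-level correlation of 0.40", with a prevalence of 14%, a standard deviation of 25%, an ICC of 0.05, 80% power and a two-sided 5% test. The stated detectable difference is 7 percentage points.

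**The concern.** With one VDC intercept, a VDC that lies above average at baseline is taken to lie above average by the same amount at 12 and 18 months. That shared amount cancels from the change, so the model's standard error is close to what it would be if all women were independent.

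A correlation over time below 1 means that VDC levels also move from one survey to the next, for reasons unrelated to the intervention. In a trial that randomises VDCs, this movement is the error against which the net change between arms has to be judged. If the model leaves it out, chance drift in 18 VDCs per arm can be read as an intervention effect. The primary comparisons at both 12 and 18 months are exposed to this.

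**Working it through.** **Inputs** (Sample size and power): g = 18 VDCs per arm (36/2); m = 40 women per VDC, taken as 40 at each survey; prevalence 0.14; SD σ = 0.25; ICC 0.05; correlation 0.40.

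**Step 1: reproduce the plan's 7 points.** Detectable difference = (critical value + power quantile) × SE, for a difference between arms in change.
- VDC variance: σ_g² = 0.05 × 0.0625 = 0.003125.
- Sampling variance of a VDC mean: 0.95 × 0.0625 / 40 = 0.001484.
- Reading A, 0.40 is the correlation of observed VDC means: SE² = 4(0.003125 + 0.001484)(0.60)/18 = 0.000615, SE = 0.0248. The detectable difference is 6.95 points (z), 7.04 (t, 70 df) or 7.15 (t, 34 df).
- Reading B, 0.40 is the correlation of the underlying VDC effects: SE² = 4(0.003125 × 0.60 + 0.001484)/18 = 0.000747, SE = 0.0273. The difference is 7.65 points (z) or 7.88 (t, 34 df).
- One VDC intercept only (correlation 1): SE² = 4(0.001484)/18 = 0.000330, SE = 0.0182. The difference is 5.1 points (z) or 5.2 (t, 34 df).

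Reading A gives the stated 7. The intercept-only variance does not, so the power calculation allowed for movement of VDCs over time that the named analysis model lacks.

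**Step 2: true variance against the model's variance.** Set the total variance to 1; σ and the common factor 4/g cancel from the ratio. With r the correlation of VDC effects:
- V_true = 0.05(1 − r) + 0.95/40
- V_model = [0.95 + 0.05(1 − r)]/40, because the intercept-only model treats the survey-specific VDC part as noise between women.

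Reading B, r = 0.40: V_true = 0.03 + 0.02375 = 0.05375; V_model = 0.98/40 = 0.0245; ratio 2.19. The SE is too small by a factor √2.19 = 1.48, and intervals have 1/1.48 = 68% of the proper width.

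Reading A: the implied r is 0.40 × (0.05 + 0.02375)/0.05 = 0.59. V_true = 0.0205 + 0.02375 = 0.04425; V_model = 0.9705/40 = 0.02426; ratio 1.82. The SE is too small by a factor 1.35, and intervals have 74% of the proper width.

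**Step 3: type I error** = 2[1 − Φ(c√(V_model/V_true))], with c = 1.96 or the t critical value. This was checked by fitting a random-intercept logistic model to simulated null trials with 36 VDCs, 40 women per survey, prevalence 14% and ICC 0.05 on the proportion scale (8,000 trials per case; 2,000 for r = 1).

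| Case | Formula: z / t 34 df | Simulated: z / t 34 df |
|---|---|---|
| Reading A (r = 0.59), two surveys | 14.7% / 13.2% | 14.8% / 13.4% |
| Reading B (r = 0.40), two surveys | 18.6% / 17.0% | 19.4% / 17.5% |
| Reading B, three surveys | not computed | 19.1% / 17.7% |
| r = 1 (control) | 5.0% / 4.2% | 5.7% / 4.7% |

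The control shows that the excess comes from the missing term. With 17 df (18 pairs − 1) the simulated values are still 12.1% (A) and 15.8% (B), so the reference distribution does not repair the SE. In the same simulated trials with r below 1, a t test on VDC-level changes (34 df) gave 4.6 to 5.0%.

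**Step 4: milder inputs**, with the correlation applied to VDC effects. ICC 0.02 and r = 0.40 give 11.3% (z) or 10.0% (t, 34 df) by simulation, and 10.6% or 9.4% by formula. ICC 0.05 and r = 0.80 give 10.5% or 9.3% by simulation, and 9.8% or 8.7% by formula.

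**The case against.** **The text does not say that this is the only random effect.** The article condenses the analysis into a paragraph, the full analysis plan is not shown, and the power section shows that correlation over time was considered. A VDC-by-time term may be intended. That limits what can be said about the analysis that will be run: a reader might infer that the trial is certain to use a mis-specified test, and the article does not establish that. It does not remove the point. The fixed effects are listed in full, one random effect is named beside them, and that model conflicts with the article's own power assumptions.

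**A reader might infer that about one in five null trials would be declared positive.** That is the upper end. It needs Reading B, which does not reproduce the 7 points, and it takes as true an ICC and a correlation that the plan calls conservative. Step 4 shows smaller inflation. If ICC 0.02 is combined with Reading A, the formula gives only 6.0% (z) or 5.1% (t, 34 df), so the inflation nearly vanishes there.

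**Matching is not in the calculation.** VDCs were paired partly on location. Local shocks shared within a pair would cancel from the arm contrast. As an assumption only, a within-pair correlation of 0.3 in the survey-specific effects gives about 12% (Reading A: ratio 0.0381/0.02426 = 1.57) or 15% (Reading B: ratio 0.04475/0.0245 = 1.83), using z. This softens the result without removing it. Ward-level clustering was not modelled either.

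**The added term is not a perfect cure.** A small check (400 simulated trials) with a VDC-by-time effect gave about 7%. A claim that the extended model holds exactly 5% is not supported.

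**Conclusion.** The concern stands. Followed as written, the primary model contradicts the error structure on which the trial was powered, and its test of time by condition is anti-conservative. Under the plan's ICC of 0.05, correlation of 0.40 and 40 women per VDC per survey, the type I error of the nominal 5% test is about 13 to 19%. It is 13 to 15% on the reading of 0.40 that reproduces the 7 points, and 17 to 19% on the other. Intervals are about one quarter to one third too narrow. A milder ICC or correlation of VDC effects brings the figure to about 9 to 11%.

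These sizes rest on the literal model (one VDC intercept, no robust variance), different women treated as independent between surveys, and no allowance for pairs or wards. They do not depend on the 25% SD.

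**What to change.** State in the Statistical analysis section that the model has random effects for VDC and for VDC by time (cluster-period), and that the baseline-to-12-month and baseline-to-18-month contrasts are each tested with VDC-level degrees of freedom: 36 − 2 = 34, or 18 − 1 = 17 if the pairs are kept in the analysis.

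Prespecify an analysis of VDC-level changes in prevalence as a check, because it held its size near 5% with 36 clusters. In the Sample size and power section, say whether 0.40 is the correlation of observed VDC means or of VDC effects.

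If the full analysis plan already has the VDC-by-time term, correcting the article's sentence is enough. The cost is one model term and one supporting analysis, with no new data. Under the plan's inputs the standard error grows by a factor of about 1.35 to 1.48 over the intercept-only model, so intervals widen. On Reading A that returns the detectable difference from about 5 points to the 7 that the plan states.

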### Allocation concealment mechanisms

Baseline community survey recruitment and administration occurred prior to randomizing study sites in order to minimize bias in recruitment. Further, the informed consent forms did not identify which study-related activities would be implemented in their community. While subsequent survey data collection will inherently come after treatment allocation, the study’s primary outcome stems from the community-based surveys. These individuals will be interviewed by the data collection firm who has no role in the project, enabling the study to keep community survey participants and outcome assessors blind to site allocation. LDG participants cannot be blinded due to the nature of their engagement. Individual recruiters, outcome assessors and data analysts will be blinded to treatment assignment.

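### At the plan's over-time correlation of 0.40, the time-by-condition contrast is valid but inefficient; adjusting for the pre-randomisation baseline would cut its variance by about 30%

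*Protocol article*

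**What the plan says.** In the protocol article, the Statistical analysis section estimates treatment effects with logistic mixed models that compare the change from baseline to each follow-up between arms. It states: "Time, condition, and time by condition interaction will be fit as fixed effects". The only random effect named is one for VDC. Covariate adjustment is limited to socio-demographic characteristics, and only if confounding is detected. Baseline IPV is not a covariate, and the arms are not constrained to a common baseline mean.

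The Sample size and power section describes the design: "We have 36 units of randomization (VDCs) and 40 randomly sampled persons within each unit". It sets the stability of VDC prevalence over time with "Assuming a conservative over-time group-level correlation of 0.40" and the clustering with "a conservative intra-class correlation of 0.05". With a standard deviation of 25%, 80% power and two-sided 5% alpha, it gives a detectable difference of 7 percentage points.

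The Allocation concealment mechanisms section states: "Baseline community survey recruitment and administration occurred prior to randomizing study sites".

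**The concern.** With condition in the model as a free main effect, the arms may differ at baseline by any amount, and the interaction subtracts that estimated difference in full. Women are sampled afresh at each round, so the only over-time correlation available is at VDC level. When that correlation is below 0.5, subtracting a noisy baseline adds more variance than it removes.

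Because baseline was surveyed before allocation, both arms have the same expected baseline prevalence, and any observed difference is chance. The model does not use this. At stake is precision in a 36-cluster trial, from data the trial collects anyway.

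**Working it through.** **Inputs** (Sample size and power section, except as noted): SD 0.25; ICC 0.05; m = 40 women per VDC; 18 VDCs per arm (36, one of each pair to treatment, from Pair-matching); over-time correlation 0.40; two-sided 5% alpha and 80% power, so the multiplier is 1.960 + 0.842 = 2.802.

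**Step 1: variance of a VDC mean.** v = SD² × [ICC + (1 − ICC)/m] = 0.0625 × (0.05 + 0.02375) = 0.004609. Comparing follow-up alone has variance (2/18) × v = 0.000512, SE 2.26 points.

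**Step 2: reproduce the plan's figure.** The change contrast has variance (2/18) × v × 2(1 − r). At r = 0.40 this is 0.000512 × 1.20 = 0.000615, SE 2.48 points. The detectable difference is 2.802 × 2.48 = 6.95 points (7.15 with t on 34 df). This matches the stated 7%, so the change contrast with 0.40 as the correlation of VDC means appears to be the basis of the sample size.

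**Step 3: the other reading of 0.40.** If 0.40 is the correlation of the underlying VDC effects, the correlation of observed means is 0.40 × 0.05/0.07375 = 0.271. The change contrast then gives 7.65 points, a worse match to 7%.

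**Step 4: compare the contrasts.** Relative to follow-up alone, the change contrast has variance 2(1 − r) and the baseline-adjusted contrast 1 − r². Their ratio, adjusted to change, is (1 + r)/2. The SD cancels. Estimating the adjustment slope from 36 VDCs multiplies the adjusted variance by about 1 + 1/32, or 1.031.

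| r of VDC means | change / follow-up only | adjusted / follow-up only | adjusted / change | cut against change | cut after slope cost |
|---|---|---|---|---|---|
| 0.271 | 1.46 | 0.93 | 0.64 | 36% | 34% |
| 0.40 | 1.20 | 0.84 | 0.70 | 30% | 28% |
| 0.50 | 1.00 | 0.75 | 0.75 | 25% | 23% |
| 0.678 | 0.64 | 0.54 | 0.84 | 16% | 13% |

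The last row is the correlation implied by a VDC intercept as the only random effect: 0.05/0.07375 = 0.678.

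**Step 5: detectable difference on the plan's inputs** (normal approximation, before slope cost):
- r = 0.40: 6.95 points (change), 6.34 (follow-up only), 5.81 (adjusted). With t quantiles, change falls from 7.15 to 5.99.
- r = 0.271: 7.65, 6.34 and 6.10 points.

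**Step 6: check with binary data.** A simulation with beta-binomial clusters, prevalence 14%, ICC 0.05 and 40,000 replicates gave change to follow-up-only variance ratios of 1.22 and 1.48 under the two readings. Adjustment cut the change variance by 28% and 35%, in line with the last column of the table.

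**The case against.** The strongest reply is that the plan is coherent. The stated aim is a greater reduction in cluster-level IPV, the effect is defined as change from baseline, and the sample size matches that contrast. A time-by-condition interaction is a conventional analysis of repeated cross-sections. All of this stands: the point concerns efficiency, and the documents do not support a reader who infers bias or an invalid test.

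The size also depends on a planning value that the protocol itself calls conservative. Above r = 0.5 the change contrast is no longer worse than ignoring baseline, and at 0.68 adjustment saves 16%. That stands too. It does not remove the point: (1 + r)/2 is below 1 for every r below 1, and after the slope cost adjustment still wins until r is about 0.94 (from (1 + r)/2 × 33/32 = 1).

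Two further inferences are tempting and should not be drawn:
- **That adjustment gains 30% over ignoring baseline.** That comparison gives only 7 to 16%, before the slope cost. The larger figure is relative to the planned contrast.
- **That the trial is shown to be under-powered.** On the stated inputs the change contrast does reach about 7 points. Whether an SD of 25% suits a binary outcome at 14% prevalence, where √(0.14 × 0.86) = 0.347, is a separate question. It cancels from every ratio here.

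**Conclusion.** The point holds as an avoidable loss of precision. At the plan's correlation of 0.40, on the reading that reproduces its 7%, the planned contrast has 1.20 times the variance of follow-up alone. Baseline adjustment would reduce the planned contrast's variance by about 30%, or 28% net of slope estimation. If 0.40 refers to VDC effects, the reduction is 34 to 36%, but that reading fits the stated 7% less well.

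The conclusion rests on three assumptions:
- The ratios are on the linear VDC-mean scale, not the log-odds scale.
- The same correlation applies at 12 and 18 months; the protocol gives only one value.
- Pair-matching is ignored. If matching already removes stable differences between VDCs, the remaining correlation is lower. The change contrast then compares worse with follow-up alone, and the gain of adjustment over follow-up alone shrinks.

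**What to change.** Make the primary analysis at each follow-up one of the following, chosen in advance:
- a logistic mixed model comparing arms at follow-up, with the VDC's baseline IPV prevalence as a covariate and a VDC random effect; or
- a model of all rounds with a common baseline mean (time and condition-by-follow-up terms, no condition main effect) and both VDC and VDC-by-time random effects.

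The two are similar but not identical in scale and weighting, so one should be named. In the second, the VDC-by-time effect is essential. A VDC intercept alone treats cluster effects as perfectly stable, which contradicts a correlation of VDC effects below 1 and would over-weight baseline.

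Keep the planned time-by-condition model as a sensitivity analysis. The change is to analysis wording and needs no new data. For covariate adjustment, the statistical cost is one cluster-level degree of freedom and about 3% of variance.

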### Performance monitoring and auditing

The project has an extensive monitoring plan and an accompanying process evaluation. It also has a Technical Advisor assigned by the What Works Global Program who meets weekly with Equal Access’ Technical Advisor for regular updates that are fed back to the Global Program leadership, along with quarterly reports, all of which support ongoing accountability. An independent audit is not anticipated.

### Ethics and dissemination

The study adheres to international guidelines for the protection of participants and staff involved in research on violence against women [42] and has a data and safety monitoring plan which details procedures and reporting obligations regarding expected risks and planned protections, confidentiality and data security, and adverse events with oversight provided by an Independent Monitor who is unaffiliated with the study. This study will be stopped prior to its completion if it is associated with adverse effects that call into question the safety of the participants enrolled. Institutional Review Board (IRB) approval has been received from the University of Minnesota, where the PI was based when the study was funded, Emory University, where the PI is currently based, George Mason University where the co-investigator is based and the Nepal National Health Research Council (NHRC). Permission was also received from the District Development Committees representing Nawalparasi, Kapilvastu and Chitwan.

Written informed consent will be sought from all participants prior to randomization, except for activities related to LDG participation for which recruitment occurred after treatment allocation. VDRC field officers who are involved in recruiting will read the statement the because of the significant number of illiterate individuals in Nepal, most of whom are women. Once participants have agreed to participate in the study, the participant and the person obtaining the consent will sign the consent document. Illiterate individuals will be asked to place an “X” instead of their signature. VDRC field officers will obtain informed consent during the recruitment visit. Informed consent will be reaffirmed by the enumerator by reading a summary of participant rights just prior to administering the survey.

Research indicates that social norms campaigns may have perverse effects [13] including raising awareness of VAWG to the point where it is perceived as being ubiquitous and, thus, more acceptable. We take several steps to address this including engaging community actors in social norms change, such as addressing injunctive rather than descriptive norms, engaging community stakeholders at all levels and involving diverse genders in the development of programming [13, 43]. Additionally, raising awareness of VAWG and available services may encourage women to seek help [44]. The study entails an extensive safety plan, including partnering with key violence advocate and service-providing organizations to ensure the availability of counselling and immediate response. All study participants will be made aware of other resources for women and couples in their areas.

